### **6.1.3 Study Discontinuation**

The number and percentages of participants who completed the study, as well as the reasons for non-completion, will be displayed in a table overall and by site and by randomization arm and by follow-up period.

Time from enrollment to study discontinuation and time from crossover to study discontinuation will be summarized using Kaplan-Meier curves overall and by arm.

### **6.2 Treatment Exposure**

Treatment exposure will be defined by randomization arm from the parent protocol and number of doses received. The number and percentage of participants who received no doses, one dose, and two doses will be displayed in a table overall and by site and randomization arm.

## **7. BASELINE DATA**

Baseline demographic characteristics of the participants, such as site, state, age, sex, randomization arm, race, exposure risk information such as whether “the subject is a student attending school in person” will be displayed in a table overall and by site, and in a table overall and by randomization arm. Baseline is defined as time of enrollment into SNIFF. Demographic characteristics are collected in the parent study with a collection time that may not align with enrollment into SNIFF; therefore, baseline characteristics will be determined from the data collected most recently before enrollment into SNIFF.

The set of characteristics collected at baseline (including randomization arm) in the parent study will be compared between those who enrolled in SNIFF versus those who did not.

## **8. SAFETY ANALYSES**

Limited safety data were collected as part of the SNIFF study and are expected to be low in frequency. If applicable, summaries of adverse events will include a cumulative listing of adverse events and a table displaying the total number of adverse events by severity grade and relationship to study product.

## 9. PRIMARY EFFICACY/EFFECTIVENESS ANALYSES

### 9.1 Descriptive measures of SARS-CoV-2 acquisition:

*Table 1 Table for use when summarizing incident outcomes, including infection, overall and with and without COVID-defining symptoms.*

| Randomization arm  | Exposure                         | Number of participants | Number of incident endpoints | Person-years | Incidence rate (95% CI) |
|--------------------|----------------------------------|------------------------|------------------------------|--------------|-------------------------|
| Vaccine -> Placebo | Two doses of vaccine             |                        |                              | See note 2   |                         |
| Placebo -> Vaccine | Single dose of vaccine           |                        |                              | See note 1   |                         |
|                    | Two doses of vaccine             |                        |                              | See note 2   |                         |
|                    | Unvaccinated (two placebo doses) |                        |                              | See note 3   |                         |

Note 1: Total number of person-years post first dose and pre first of second dose in the crossover period, infection (maybe due to RT-PCR or antibody evidence of infection as per endpoints in analyses described below) or censoring.

Note 2: Total number of person-years post second dose and pre first of infection (maybe due to RT-PCR or antibody evidence of infection as per endpoints in analyses described below) or censoring.

Note 3: Total number of person-years post second dose of placebo and pre first of infection (maybe due to RT-PCR or antibody evidence of infection as per endpoints in analyses described below) or censoring.

The table above will be replicated by time periods, stratifying by calendar month as well as pre and post crossover. Results will be plotted over time. Additional calendar periods may be defined by predominant variant at the site with further stratification by the variant associated with the endpoint, recognizing that not all infections have enough virus present to be sequenced.

#### **Descriptive Plots**

Kaplan-Meier curves will be used to display incidence of infection across study groups. Multiple curves will be produced, corresponding to the four exposure groups in [Table 1](#) for the PAS, PAS2 and PCAS. Endpoint definitions follow in the analysis descriptions for primary and secondary analyses.

Each of these sets of plots will be produced once where the time scale is calendar time and once where the time scale is study time (time since enrollment).

### 9.2 Primary Objective: Prevention of Infection

#### Primary analysis

Endpoint: SARS-CoV-2 detected by RT-PCR on self-collected SNIFF-provided nasal swabs, right-censored at the last negative test at or before the earliest of the second dose of the crossover vaccination series (vaccine or placebo), 4 weeks post first crossover dose (applicable for cases where the second dose in the crossover period is missed or late), termination, or receipt of EUA vaccine.

Data sets: Primary analyses set; supported by analyses on the mITT set

Approach: Incidence of SARS-CoV-2 infection will be analyzed using a Cox Proportional Hazards model using follow-up time through 4 weeks post crossover. Calendar time will not be accounted for in the primary analysis since enrollment was completed in a short window of time. This analysis only counts infections until the second dose of the crossover series. Follow-up time may be right-censored earlier if a participant receives an EUA vaccine or otherwise is terminated early from the study. Randomization arm will be merged from the primary study database. Efficacy will be estimated as 1-HR (hazard ratio) from a Cox proportional hazards model. The primary analysis will not use any endpoint information collected in the parent study. This analysis will only include randomization as a covariate. The proportional hazards assumption will be assessed graphically.

#### Sensitivity analysis 1

The analysis will be repeated counting follow-up time up to 2 weeks post first dose of the crossover series.

Endpoint: SARS-CoV-2 detected by RT-PCR on self-collected SNIFF-provided nasal swabs, right-censored at the last negative test at or before the earliest of the second dose of the crossover series (vaccine or placebo), 2 weeks post first crossover dose (applicable for cases where the second dose is missed or late), termination, or receipt of EUA vaccine.

#### Supporting analysis 1

If any participants are identified as having infection in the parent study but not in the SNIFF study, the primary analysis will be repeated by revising the primary endpoint to include the first time to SARS-CoV-2 infection as defined in the parent study or SNIFF.

Endpoint: SARS-CoV-2 detected by RT-PCR on self-collected SNIFF-provided or Novavax-provided nasal swabs, right-censored at the collection time of the last RT-PCR negative swab at or before the earliest of the second dose of the crossover series (vaccine or placebo), 2 weeks post first crossover dose (applicable for cases where the second dose is missed or late), termination, or receipt of EUA vaccine.

Note: Novavax-provided swabs may either be self-collected at home or collected at study visits.

#### Supporting analysis 2

Because the SNIFF population is a subset of the parent study and was selected post-randomization from the parent study, the primary analysis and supporting analysis 1 will be repeated with adjustment for potential confounders. These will be selected from baseline variables that are univariably (adjusted for state) predictive of risk of acquisition of infection or differ by randomization arm with  $p < 0.10$ . If there are inadequate numbers of participants per state, state may be dropped as an adjustment variable.

#### Supporting analysis 3: Delta variant analysis

Supporting analysis 2 will be repeated with each person's follow-up time starting at the time at which delta variant became over 80% predominant in their state according to nextstrain.org. Adjustment for covariates will be included as per supporting analysis 2.

## 10. SECONDARY ENDPOINTS

### 10.1 Secondary Objective: Prevention of Asymptomatic/Very Mild Symptomatic Infection (A/VMS)

Endpoint: SARS-CoV-2 detected by RT-PCR on self-collected SNIFF-provided nasal swabs, right-censored at the last negative test at or before the earliest of: a COVID-defining endpoint from the parent trial, 4 weeks post first crossover dose, termination, or receipt of EUA vaccine.

Data sets: Primary analyses set; supported by analyses on the mITT set

Approach: We will use the approach presented for the primary outcome to ensure proper accounting for variable follow-up time due to early crossover. Data sources from the Phase 3 trial (e.g., study product assignment and clinical symptomatology, including adjudicated COVID-19 illness endpoints) will be accessed to ascertain the symptomatology of participants who are RT-PCR-positive in the ancillary study.

Table 1 in Section 9.1 will also be completed for this endpoint.

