#### **Secondary Objective: Prevention of Asymptomatic/Very Mild Symptomatic Infection (A/VMS)**

Endpoint: SARS-CoV-2 detected by RT-PCR on self-collected nasal swabs absent COVID-defining symptoms compatible with primary endpoint

Population: Intention to Treat

Incident infections that do not meet the COVID-19 illness endpoint definition (within a pre-defined number of days) will count towards the endpoint of A/VMS infection. Vaccine efficacy will be calculated as  $1 - \frac{(\text{number of endpoints in vaccine arm})}{(\text{number in vaccine arm})} / \frac{(\text{number of endpoints in placebo arm})}{(\text{number in placebo arm})}$ . If rates of censoring are high, either due to drop out or early cross-over, this analysis will instead be conducted using time to event analyses, such as Cox Proportional Hazards models. Details will be contained in the Statistical Analysis Plan. The analysis will be conducted on the Intention to Treat population. Data sources from the Phase 3 trial (e.g., study product assignment and clinical symptomatology,

---

including adjudicated COVID-19 illness endpoints) will be accessed to ascertain the symptomatology of participants who are PCR-positive in the ancillary study.

Exploratory analyses conducted on the Intention to Treat and Incident Infections populations to meet the exploratory objectives of this protocol will be detailed in the Statistical Analysis Plan.

---

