| Secondary                                                                                                                                               |                                                                                                                                                                                                                                                                                                                                                                                                      |
| 
 
To estimate the efficacy of SARS-CoV-2 rS/M1 vaccine against asymptomatic/ very mildly symptomatic infection
 
 | 
 
RT-PCR-confirmed SARS-CoV-2 infection detected in nasal swabs collected twice weekly from the day 21 visit or thereafter, until the second dose in the second vaccination (crossover) series, without COVID-19 illness as defined in the primary Phase 3 study endpoint. The COVID-19 disease endpoint will be defined in the main study database.
 
 |
| 
 
To determine the durability of efficacy of SARS-CoV-2 rS/M1 vaccine against infection
 
                        | 
 
RT-PCR-confirmed SARS-CoV-2 infection detected in nasal swabs collected twice weekly from the crossover dose 2 visit (or thereafter) until ancillary study end among the group who initially received vaccine compared to the group who initially received placebo
 
                                                                                 |

|                                                                                                                                                                                                                                         |                                                                                                                                                                                                                                                                                                                                                                                                                                                                                                                    |

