### 10.3 Secondary Objective: To determine the durability of efficacy of SARS-CoV-2 rS/M1 vaccine against asymptomatic/very mildly symptomatic infection

Endpoint: SARS-CoV-2 detected by RT-PCR on self-collected SNIFF-provided nasal swabs, right-censored at the last negative RT-PCR test at or before the earliest of: a COVID-defining endpoint from the parent trial, termination or receipt of EUA vaccine.

Data set: Post crossover analyses set (PCAS)

Approach: The analysis in section 10.2 will be repeated for this outcome.

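### SAP 10.1 and 10.3 use COVID-19 illness only to end follow-up, so a positive swab before illness counts as asymptomatic/very mild infection, against SAP 2.2 and protocol 10.3

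*Supplement*

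**What the plan says.** Four places in the current documents bear on this endpoint.

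- **SAP v2.0, 2.2** defines it as RT-PCR-confirmed infection "until the second dose in the second vaccination (crossover) series, without COVID-19 illness as defined in the primary Phase 3 study endpoint".
- **Protocol v4.0, 10.3** says: "Incident infections that do not meet the COVID-19 illness endpoint definition (within a pre-defined number of days) will count". It gives no number and passes the matter on: "Details will be contained in the Statistical Analysis Plan".
- **SAP v2.0, 10.1** sets the operational rule. The event is SARS-CoV-2 detected on a SNIFF swab, "right-censored at the last negative test at or before the earliest of: a COVID-defining endpoint from the parent trial". The other censoring triggers are 4 weeks after the first crossover dose, termination, and receipt of an EUA vaccine. The section adopts the primary-outcome approach and adds that Phase 3 data "will be accessed to ascertain the symptomatology of participants who are RT-PCR-positive in the ancillary study".
- **SAP v2.0, 10.3** carries the same rule into the durability analysis: "right-censored at the last negative RT-PCR test at or before the earliest of: a COVID-defining endpoint from the parent trial".

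The exploratory composite in SAP 2.2 and 11.4 is A/VMS infection with pre-symptomatic infection added to it.

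**The concern.** A censoring rule can only remove events that come after the censoring trigger. A pre-symptomatic positive comes before the illness date, so the rule in 10.1 leaves it in as an event, and nothing later in the section takes it out. The status of a symptomatic infection then depends on whether a swab happened to be taken, and to be positive, before the illness date.

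The secondary objective exists to estimate efficacy against infection that does not become illness. If symptomatic infections enter the count, the estimate is a mixture of that efficacy and efficacy against illness. The exploratory composite shows that A/VMS was meant to exclude pre-symptomatic positives: otherwise adding them would change nothing. Because the SAP never supplies the number of days that the protocol defers to it, two analysts could derive different endpoints from the same plan.

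Section 10.1 also departs from 2.2 on when follow-up stops. SAP 2.2 ends it at the second crossover dose. The list in 10.1 does not contain that dose.

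**Working it through.** **1. Apply the rules to two swab sequences.**

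| Sequence | SAP 10.1 | SAP 2.2 | Protocol 10.3 |
|---|---|---|---|
| Negative day 0, positive day 3, illness endpoint day 5 | A/VMS event on day 3 | Not A/VMS | Not A/VMS with any window of 2 days or more |
| Negative day 0, illness endpoint day 2, first positive day 3 | Censored at day 0 | Not A/VMS | Not A/VMS with any window of 1 day or more |

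Both sequences are symptomatic infections. Section 10.1 separates them by swab timing.

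**2. Reproduce the counts that size the issue.** The inputs are from Table S2, PAS, censored at crossover dose 2. Vaccine: 13 infections, 87.2 person-years, 4 meeting PREVENT-19 endpoints. Placebo: 21 infections, 38.7 person-years, 7 meeting them.

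Rate = 100 × events / person-years:
- vaccine 100 × 13/87.2 = 14.9, exact 95% CI 7.9 to 25.5, as reported;
- placebo 100 × 21/38.7 = 54.3, CI 33.6 to 82.9; the table has 54.2, a difference explained by rounded person-years.

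Crude VE = 1 − (13/87.2)/(21/38.7) = 72.5%, against 73.5% in the table.

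**3. Bound the misclassification.** The infections at risk are those meeting PREVENT-19 endpoints: 4 + 7 = 11 of 34 (32%), or 4/13 = 31% of vaccine and 7/21 = 33% of placebo infections. The A/VMS count lies between 34 − 11 = 23 and 34. Individual times are not given, so full person-time is kept throughout.

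| Illness cases counted as A/VMS | Vaccine | Placebo | Crude VE (95% CI where computed) |
|---|---|---|---|
| All 11 | 13 | 21 | 72.5% (45.1 to 86.2) |
| None | 9 | 14 | 1 − (9/87.2)/(14/38.7) = 71.5% (34.1 to 87.7) |
| All 4 vaccine, no placebo | 13 | 14 | 1 − (13/87.2)/(14/38.7) = 58.8% |
| No vaccine, all 7 placebo | 9 | 21 | 1 − (9/87.2)/(21/38.7) = 81.0% |

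In the mITT set, 13 of 44 infections are at risk (4/16 and 9/28). Crude VE is 74.0% with all counted and 71.3% with all removed.

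**4. How many positives might precede illness?** The documents do not say how long before onset virus is detectable, so a window of 1 to 4 days is an assumption. SAP 6.1.2 expects swabs on Mondays and Thursdays, and Table S3 shows 63.0% of expected windows received. For windows up to 3 days, at most one scheduled swab falls in the window. The share of symptomatic cases with a swab in it is 2 × days / 7, multiplied by compliance. For 4 days, one onset day in seven has two swabs in the window: at 63% the share is 6/7 × 0.63 + 1/7 × (1 − 0.37²) = 66%.

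| Assumed window | Full compliance | 63% compliance |
|---|---|---|
| 1 day | 29% | 18% |
| 2 days | 57% | 36% |
| 3 days | 86% | 54% |
| 4 days | 100% | 66% |

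At 63% compliance that is about 2 to 7 of the 11 (0.18 × 11 = 2.0; 0.66 × 11 = 7.3).

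**5. Crossover dose 2.** SAP section 1 puts the second crossover injection 21 days after the first. The list in 10.1 stops at 4 weeks, so read literally it adds 28 − 21 = 7 days, during which placebo-first participants have had both active doses.

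**The case against.** The strongest reply is that this is a drafting gap. SAP 2.2 states the right endpoint, and 10.1 provides for ascertaining symptoms in positives, a step with little purpose unless positives are then classified. Table 1 of the SAP, required for this endpoint, is meant to show infections with and without COVID-defining symptoms. That much stands: a reader might infer that the plan decided to count symptomatic cases as A/VMS, and the documents do not support it. But neither the ascertainment sentence nor Table 1 gives an exclusion rule or a window.

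A second reply is that censoring at the last negative test before illness sends the first sequence back to day 0 and so drops the pre-symptomatic positive. This is strained. The primary endpoint in 9.2 uses the same phrase, and read that way it would erase primary events that are followed by crossover dose 2. Protocol 10.3, in its primary analysis, reserves last-negative censoring for participants who are never positive. The illness trigger in 10.1 does differ in kind from the primary triggers, so some ambiguity remains; that is itself a reason to write the rule out.

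A third reply concerns size, and it stands. One can construct cases in which the mixture inflates VE. Assume half of placebo infections are symptomatic, VE is 90% against illness and 40% against A/VMS, and half of symptomatic cases are misclassified: reported VE becomes 1 − (0.30 + 0.025)/(0.50 + 0.25) = 57%. Table S2 does not look like that. A third of placebo infections met the illness endpoint, and crude VE against illness is 1 − (4/87.2)/(7/38.7) = 74.6%, close to the 71.5% for the remainder. With half of each arm's illness cases counted, VE is 1 − (11/87.2)/(17.5/38.7) = 72.1%, a shift of 0.6 points.

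On crossover, the approach that 10.1 adopts does stop at the second dose, so the intended cut-off is fairly clear. The explicit list still conflicts with it.

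**Conclusion.** The conflict is real: the operational rule in 10.1 and 10.3 contradicts SAP 2.2 and protocol 10.3, and the number of days the protocol calls for is missing. The main harm is that the endpoint does not cleanly separate A/VMS from illness. It affects secondary endpoints only; the primary analysis is untouched.

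In the PAS, 11 of 34 is an upper bound. A reader might take 34 against 23 events (34/23, or 48% more) as the actual excess, but that requires every illness case to have been swab-positive first, and no document says how many were. The bound also assumes that the PREVENT-19 column of Table S2 refers to the illness belonging to the same infection. The 18% to 66% range rests on the assumed detection window and on average compliance applied to every case.

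Overstated VE is possible but not shown. Counting or removing all 11 moves crude VE by one point; only an uneven split between arms would take it towards 58.8% or 81.0%. Nor do the documents show which rule the final analysis used. A reader might also infer that the asymptomatic-to-symptomatic comparison in 11.5 inherits the error, but 11.5 names its own ratio and draws symptoms from the Phase 3 database, so that does not follow.

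**What to change.** In SAP 10.1 and 10.3:

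- Define an A/VMS event as a first SNIFF RT-PCR positive with no adjudicated parent COVID-19 endpoint within a stated number of days before or after it. State the number and the date used for the parent endpoint.
- Treat an infection that meets the endpoint as a competing event: censor it, state the censoring time, and estimate a cause-specific hazard.
- Repeat the analysis with shorter and longer windows as a sensitivity analysis.
- Leave pre-symptomatic positives to 11.4.

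In 10.1 only, add the second crossover dose to the censoring list so that it matches 2.2 and the primary approach. If the analysis has already been run, report which rule was used and give the other as a sensitivity analysis.

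The cost is a few lines of SAP text and one derived flag from parent-study data that SAP 3.2 already plans to merge. The downside is fewer events and a wider interval: in the PAS at most from 34 to 23 events, with the crude interval going from 45.1–86.2% to 34.1–87.7%. The look-forward also needs parent data for the full window after each first positive.

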| Crossover series  | The second series of two injections of either vaccine or placebo given at crossover and 21 days later                                                                                                                                                                                                                                                  |

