## Description of Study Product or Intervention:

Participants in the PREVENT-19 Phase 3 trial (pediatric expansion study) are randomized to receive either SARS-CoV-2 rS/M1 vaccine or placebo (2:1 allocation) on days 0 and 21. The pediatric expansion study will have a “blinded-crossover” after ~3 months of follow-up after the completion of the initial set of vaccinations. Pediatric participants will be scheduled for administration of 2 injections of the alternate study material 21 days apart. In the current protocol, no interventional product will be administered.

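### SAP 10.1 leaves the second crossover dose out of the A/VMS censoring list, in conflict with SAP 2.2 and 9.2

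*Supplement*

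**What the plan says.** SAP v2.0 describes the end of A/VMS follow-up in three places.

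- Section 2.2, in the endpoint table, counts A/VMS infections "until the second dose in the second vaccination (crossover) series, without COVID-19 illness as defined in the primary Phase 3 study endpoint".
- Section 10.1, which specifies the analysis, ends follow-up with the final negative swab up to "the earliest of: a COVID-defining endpoint from the parent trial, 4 weeks post first crossover dose, termination, or receipt of EUA vaccine". It adds: "We will use the approach presented for the primary outcome to ensure proper accounting for variable follow-up time due to early crossover".
- Section 9.2, the primary analysis to which that sentence points, censors at "the earliest of the second dose of the crossover vaccination series (vaccine or placebo), 4 weeks post first crossover dose", termination or EUA vaccine. It marks the 4-week limit as "applicable for cases where the second dose in the crossover period is missed or late". Its Approach paragraph states: "This analysis only counts infections until the second dose of the crossover series".

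Section 1 defines the crossover series as two injections "given at crossover and 21 days later". Section 2.1 describes "administration of 2 injections of the alternate study material 21 days apart", so participants first given placebo receive active vaccine at crossover.

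**The concern.** In 9.2 the 4-week limit is a backstop. In 10.1 the second crossover dose and the missed-or-late qualifier are both absent, so the backstop becomes the rule for everyone. For a participant dosed on schedule, follow-up then runs past the second crossover dose. In those days both arms have received two active doses, yet the delayed-vaccine group is still analysed as placebo.

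Three things are at stake. The A/VMS VE would include some time with no vaccinated-versus-unvaccinated contrast. Its risk window would differ from the one in 2.2 and from that of the primary VE. And the durability analysis of A/VMS in 10.3, through 10.2, takes the second crossover dose as its time origin, so one infection in the following week could count as a placebo-arm event in 10.1 and as a delayed-vaccine event in 10.3.

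**Working it through.** **Step 1. The rules side by side**

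| SAP v2.0 section | Second crossover dose ends follow-up? | Role of 4 weeks after first crossover dose |
|---|---|---|
| 2.2, A/VMS endpoint | Yes | Not mentioned |
| 9.2, primary endpoint | Yes | Only if the second dose is missed or late |
| 10.1, A/VMS analysis | Not listed | Applies to everyone |

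Table 1 in section 9.1, which 10.1 says will be completed for A/VMS, places placebo-first person-time after the second crossover dose under two doses of vaccine. The SAP itself therefore treats that week as vaccinated time. The summary of SAP changes for v2.0 lists only section 3.1, so the wording of 10.1 was carried over unchanged.

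**Step 2. Length of the overlap**

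4 x 7 - 21 = 7 days for a participant dosed on schedule. It is shorter if the second dose is late, and zero if that dose falls at or after day 28.

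**Step 3. Upper bound on added person-time**

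Inputs are from Table S2, primary analysis set (PAS), censored at the second crossover dose: vaccine 466 participants, 13 infections, 87.2 person-years (PY); placebo 216 participants, 21 infections, 38.7 PY.

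- Reproduction check on all infections: crude VE = 1 - (13/87.2)/(21/38.7) = 72.5%, against the tabulated 73.5%. The crude rate ratio is close enough to use as an illustration.
- Placebo: 216 x 7/365.25 = 4.1 PY, or 10.7% of 38.7.
- Vaccine: 466 x 7/365.25 = 8.9 PY, or 10.2% of 87.2.

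**Step 4. Effect on A/VMS VE**

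Table S2 gives no A/VMS counts. As an assumption, take infections minus those meeting PREVENT-19 endpoints: placebo 21 - 7 = 14, vaccine 13 - 4 = 9. Censored at the second dose, crude VE = 1 - (9/87.2)/(14/38.7) = 71.5%.

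No document gives a rate for the added week, so two rates are assumed:

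- (a) The overall A/VMS rates: vaccine 9/87.2 = 0.103 and placebo 14/38.7 = 0.362 per PY.
- (b) The infection rates between the two crossover doses, obtained by subtracting the Table S2 row censored at the first crossover dose and scaling by the A/VMS share: vaccine (8/24.6) x (9/13) = 0.225 and placebo (11/10.3) x (14/21) = 0.712 per PY.

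For each, the placebo arm in the added week is taken either as still unprotected (its own rate) or as protected as the vaccine arm (the vaccine rate). VE = 1 - [(9 + added vaccine events)/(87.2 + 8.93)] / [(14 + added placebo events)/(38.7 + 4.14)].

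| Assumed rate | Placebo arm that week | Added vaccine events | Added placebo events | Crude A/VMS VE |
|---|---|---|---|---|
| (a) | Unprotected | 0.92 | 1.50 | 71.5% |
| (a) | As protected as vaccine arm | 0.92 | 0.43 | 69.4% |
| (b) | Unprotected | 2.01 | 2.95 | 71.0% |
| (b) | As protected as vaccine arm | 2.01 | 0.93 | 67.1% |

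**The case against.** The strongest reply is that 10.1 adopts the primary approach in a sentence about follow-up and crossover, and that the primary approach stops at the second crossover dose. On that reading the list in 10.1 is shorthand and section 2.2 governs. This is a fair reading, and it is why the point is a conflict to be settled rather than proof that the wrong window was used. Table S2 shows no A/VMS analysis, so the rule actually applied cannot be seen.

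It does not close the matter, though. The sentence can equally be read as choosing a time-to-event model over the ratio of proportions in Protocol v4.0 section 10.3. Section 10.1 writes out its own censoring list, which is what a programmer would implement. The Approach text in 9.2 is itself mixed, since it also speaks of follow-up through 4 weeks after crossover. Protocol v4.0 section 3.3.2 gives no help either: it runs this endpoint to the end of the ancillary study.

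The second reply is that the effect is small. That stands. Seven days is a ceiling: censoring is at the last negative swab, only 63.0% of expected swab windows had a received swab (Table S3), and participants already infected, terminated or given EUA vaccine add nothing.

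Three stronger readings are tempting, and the documents do not support them.

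- A reader might infer that about a fifth of the A/VMS events would be misplaced: (2.95 + 2.01)/23 = 22%. That figure needs the placebo arm to be still unprotected, which is the case in which VE hardly moves. With full early protection the same rates give (0.93 + 2.01)/23 = 13%.
- A reader might infer that the added week falls when incidence was highest. Table S2 shows a high rate between the two crossover doses but stops at the second, and Figure S1 is not available here.
- A reader might infer that the exploratory objective in 11.5 is undermined because it compares the primary and A/VMS estimates. Section 11.5 instead splits vaccination status at the second dose, relies on a synthesising discussion, and specifies no comparison of the two hazard ratios.

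**Conclusion.** The conflict is real and remains in SAP v2.0: 10.1 as written does not match 2.2 or 9.2, and its reference to the primary approach leaves the question open. Applied literally, it adds up to 7 days per on-schedule participant, at most about 4.1 placebo and 8.9 vaccine PY in the PAS.

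The bias is modest and toward lower VE: from about 71.5% to about 71% if the placebo arm has no added protection that week, and to 67-69% if it is already as protected as the vaccine arm. For scale, the interval for primary VE in Table S2, which rests on more events, is 47.1% to 86.7%. These figures rest on A/VMS counts approximated from Table S2, on rates assumed for a week the documents do not report, on crude rate ratios in place of the Cox model, and on everyone being on schedule and swabbing.

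The main reason to act is that the endpoint should have one window, and that an infection should not be able to count as placebo in 10.1 and as delayed vaccine in 10.3.

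**What to change.** In SAP 10.1, add the second dose of the crossover series, vaccine or placebo, to the list of censoring events, and restrict the 4-week limit as 9.2 does: "applicable for cases where the second dose in the crossover period is missed or late". The A/VMS window then matches 2.2 and the primary analysis, and it ends where the 10.3 window begins. State in the results which rule was used. If A/VMS has already been analysed under the literal 10.1 list, rerun it with the corrected rule and report both.

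The cost is one clause in the SAP, at most one rerun of the secondary analysis, and possibly a few fewer A/VMS events. No new data are needed.
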